### Study Two: Feasibility Testing Phase

#### Participants and Design

In the feasibility testing phase, young people’s experiences of CAMHS while using Power Up will be compared to young people’s experiences of CAMHS without using the app. Study 2 is designed as a feasibility trial using a waitlist control design. A total of 60 young people, who are aged 11 to 19 years old, have recently been referred to CAMHS, and are presenting with emotional difficulties will be recruited to the trial. A clinician will have confirmed that the young person does not have any vulnerability that would make taking part in the study inappropriate to their context. They will also understand English well enough to provide informed consent or assent if they are younger than 16 years old. First, 30 young people will be recruited to the control phase of the trial where they will receive management as usual. Subsequently, 30 different young people will be recruited to the intervention phase of the trial where they will be given Power Up to use alongside management as usual.

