**Methods:**

In the development phase, 30 young people, parents, and clinicians will take part in interviews and focus groups to elicit opinions on an early version of the app. In the feasibility testing phase, 60 young people from across 7 to 10 London CAMHS sites will take part in a trial looking at the feasibility and acceptability of measuring the impact of Power Up on shared decision making.

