#### Procedure

Participants will be recruited in 7 to 10 London CAMHS sites. Clinicians will identify young people who are in their initial sessions in CAMHS. Young people and their parent or carer will be given information about the trial, and they will indicate to a member of CAMHS staff or the research team, through a telephone or face-to-face conversation, that they are interested in taking part in the project. For the control phase and the intervention phase, each service will be required to recruit 5 to 10 young people (for a total of 30 young people across services for each phase). This initial contact by services and subsequent recruitment by researchers will replicate the processes described in study 1.

If the young person is recruited during the control phase, they will meet with a researcher, along with their parent or carer, at a convenient time and place in the early stages of their therapy (up to the third treatment session). The researcher will take informed consent using the same procedures as described in study 1. The young person will then complete a battery of measures that take an estimated 15 minutes to complete. The young person’s parent or carer and clinicians will also complete a short questionnaire each.

Three months later all participants will be recontacted by the researchers and a time will be arranged for them to complete the same battery of measures a second time. Their clinician will also be asked to report the young person’s presenting problems, type of interventions used, number of sessions attended, number of missed appointments, and length of appointments.

Data collection for the intervention phase will replicate the control phase procedures. For those recruited to the intervention phase, the researcher will also help the young person to download Power Up onto their phone and will talk them through its functions after completing the first time measures. The young person will then be able to use Power Up as much as they want throughout their therapy at CAMHS, within and between sessions. In the intervention phase, a total of 10 to 12 young people and 10 to 12 clinicians across services will also take part in a posttrial interview where they will be asked about their experiences of and opinions on using Power Up in CAMHS.

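### Study 2 is called a waitlist control design, but it describes two different cohorts recruited one after the other, so the with/without-app comparison is confounded with calendar time and selection

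*Protocol article*

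**What the plan says.** Study Two, Participants and Design, gives the label: "Study 2 is designed as a feasibility trial using a waitlist control design". It also states the comparison to be made: "young people’s experiences of CAMHS while using Power Up will be compared to young people’s experiences of CAMHS without using the app".

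The sentences after the label describe how the groups are formed. The controls come first: "First, 30 young people will be recruited to the control phase of the trial where they will receive management as usual". The app group comes next: "Subsequently, 30 different young people will be recruited to the intervention phase of the trial where they will be given Power Up".

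The Procedure section says how participants are found ("Clinicians will identify young people who are in their initial sessions in CAMHS") and carries over the recruitment process of Study 1. That process has clinicians review patient lists, trains them to avoid selection bias, and records the numbers screened, eligible and approached. Only for intervention-phase recruits does it say that "the researcher will also help the young person to download Power Up onto their phone", and this happens after their baseline measures. All participants are measured again at three months and then debriefed.

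Planned Analysis makes the SDs and ICCs of the shared decision-making measures the primary outcome. It treats change in activation, empowerment and SDQ scores as an early sign of what the app may do. The Results section dates the start of the intervention phase to June 2017 and expects data collection to end by December 2017.

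**The concern.** In a waitlist design, the control participants wait and then receive the intervention, and they are normally enrolled alongside the people treated first. That gives a control group observed over the same period. The text after the label describes neither feature.

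The label matters because it tells the reader what kind of control the comparison has. Anyone who takes it at face value will credit the with/without-app comparison with a concurrent control. In the design described, group is fixed by when a young person is recruited. Changes in the services over time, clinicians' growing familiarity with the study and its measures, and differences in who is identified or agrees in each phase would all appear as a difference between the groups. If such a difference is read as an early sign of impact, it could be carried into the case for the later cluster trial.

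**Working it through.** **1. The stated total.** The abstract gives the size: "In the feasibility testing phase, 60 young people from across 7 to 10 London CAMHS sites will take part in a trial". The two phases give 30 + 30 = 60, which matches. The total does not settle the design, since a conventional waitlist trial could also have 30 per group. The order and separateness of the groups settle it.

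**2. Label against procedure.**

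| Feature | Waitlist control | What the article describes |
|---|---|---|
| Timing of groups | Normally enrolled together | Controls first, app group afterwards |
| Control participants later treated | Yes | Not described; three-month measures, then debrief |
| App group | May include former controls after their wait | 30 different people |
| Basis of group membership | Assigned (often at random) to immediate or delayed treatment | Phase of recruitment; no random allocation described |

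At most, it is the services that wait. That still gives a before-and-after comparison in different people.

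**3. What is tied to phase.**

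- *Calendar time.* The control phase comes first and the intervention phase began in June 2017. Nothing in the selection process addresses time.
- *Selection.* Clinicians identify participants in both phases. The procedure is the same, with training and recorded counts, but the phases are sequential and only one offers an app, so the phase will be evident to those who identify and those who agree.
- *Site.* The Procedure section asks each service to recruit in both phases, which limits confounding by site.

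**4. Which outcomes are exposed.** SDs and ICCs can be estimated without an unbiased contrast between phases, so the primary outcome is largely unaffected. The with/without-app comparison and the secondary change scores are exposed. Change scores remove stable differences in level between the cohorts, but not differences in how fast they would have changed anyway.

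**5. Scale.** The article gives no SD, alpha or power, so the bias itself cannot be calculated. Two figures in SD units give a sense of scale. Both ignore clustering by site and losses to follow-up.

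- 95% half-width for 30 versus 30: t(58) × √(2/30) = 2.00 × 0.258 = 0.52 SD.
- Chance of a nominal two-sided 5% difference when the app does nothing and the phases differ by d SD: 1 − Φ(1.96 − d/0.258) + Φ(−1.96 − d/0.258). For d = 0.3, d/0.258 = 1.16, giving about 0.212 + 0.001 = 0.213.

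| Assumed shift d (SD) | Chance of a nominal difference |
|---|---|
| 0 | 5.0% |
| 0.1 | 6.7% |
| 0.2 | 12.1% |
| 0.3 | 21.3% |
| 0.5 | 49.1% |

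The values of d are assumptions. Recruiting more people in the same way would shrink the standard error but not d.

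**The case against.** The strongest reply is that nothing is hidden. The sentences after the label set out the sequence, and the article claims neither randomisation nor concurrent controls. The primary outcome is a set of planning parameters, the secondary outcomes are worded cautiously, and effectiveness is left to a later parallel cluster trial. A sequential non-randomised design is a legitimate way to estimate SDs and ICCs. All of this stands, and it limits the point to the label and to how phase differences are read. It does not remove the point, because the article still says that experiences with and without the app will be compared.

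The selection safeguards also count. One identification process serves both phases, with bias training and recorded counts. They reduce selection bias, but they do nothing about time.

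Four stronger readings are tempting, and the article does not support them:

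- *Controls never receive the app.* The article is silent on later access, and the full protocol may provide for it. All that can be said is that none is described.
- *Eligibility differs because the app goes onto the young person's own phone.* No phone criterion is given for either phase, and nothing says that a person without a suitable phone is excluded.
- *The phases cover different seasons.* No start date is given for the control phase. The Results section says both that the project is currently in the control phase and that the intervention phase has commenced, so the phases may overlap across sites.
- *The feasibility results as a whole are undermined.* The primary outcome does not depend on the contrast between phases.

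**Conclusion.** The point holds in a limited form. The label is contradicted by the text that follows it: Study 2 as described is a non-randomised sequential study of a usual-care cohort followed by a Power Up cohort. The with/without-app comparison and the secondary change scores therefore cannot separate an app effect from calendar time or from who was identified in each phase.

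The size of the bias is unknown. The scale figures rest on 30 analysed per phase, independent observations and assumed shifts. They show only that a moderate shift would matter against a half-width of 0.52 SD. If the phases do overlap across sites, confounding with time is weaker but not removed, because group still follows from phase.

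The conclusion on the label would change only if the full protocol says that controls later receive the app, and the article should then say so. Even then, the stated comparison would remain sequential and non-randomised.

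**What to change.** - Replace the label with wording such as: a non-randomised, sequential two-cohort feasibility study (usual care, then Power Up). If controls do receive the app later, state when.
- State that between-phase differences, including those in the secondary outcomes, are descriptive and are not estimates of an app effect.
- Present any phase comparison adjusted for site and for the baseline score already collected. That score is taken before the app is downloaded, so it is a sound covariate. With the 10 sites now recruited, site as a fixed effect leaves 60 − 1 − 1 − 1 − 9 = 48 residual degrees of freedom (intercept, phase, baseline, sites) if all are analysed. A site that recruits in only one phase adds nothing to the adjusted contrast. Adjustment handles site mix and baseline imbalance, but not time.
- Report the screened, eligible and approached counts separately by phase, so that readers can see whether selection shifted.

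The cost is a change of wording, one adjusted model and one table built from data already planned. No new data are needed, and the change is still possible with recruitment under way. The downside is a more modest claim about what the comparison shows.

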#### Procedure

Participants will be recruited in 7 to 10 London CAMHS sites. Clinicians will identify young people who are in their initial sessions in CAMHS. Young people and their parent or carer will be given information about the trial, and they will indicate to a member of CAMHS staff or the research team, through a telephone or face-to-face conversation, that they are interested in taking part in the project. For the control phase and the intervention phase, each service will be required to recruit 5 to 10 young people (for a total of 30 young people across services for each phase). This initial contact by services and subsequent recruitment by researchers will replicate the processes described in study 1.

If the young person is recruited during the control phase, they will meet with a researcher, along with their parent or carer, at a convenient time and place in the early stages of their therapy (up to the third treatment session). The researcher will take informed consent using the same procedures as described in study 1. The young person will then complete a battery of measures that take an estimated 15 minutes to complete. The young person’s parent or carer and clinicians will also complete a short questionnaire each.

Three months later all participants will be recontacted by the researchers and a time will be arranged for them to complete the same battery of measures a second time. Their clinician will also be asked to report the young person’s presenting problems, type of interventions used, number of sessions attended, number of missed appointments, and length of appointments.

Data collection for the intervention phase will replicate the control phase procedures. For those recruited to the intervention phase, the researcher will also help the young person to download Power Up onto their phone and will talk them through its functions after completing the first time measures. The young person will then be able to use Power Up as much as they want throughout their therapy at CAMHS, within and between sessions. In the intervention phase, a total of 10 to 12 young people and 10 to 12 clinicians across services will also take part in a posttrial interview where they will be asked about their experiences of and opinions on using Power Up in CAMHS.

At the end of their involvement in the trial, participants will be debriefed by a researcher. All participants will be offered 5 pounds (US $6.63) travel reimbursement at the end of their involvement in the study. They will be given contact details for the researchers, should they wish to ask any questions or withdraw their data.

### Measures

#### Demographic Characteristics

Participants will be asked to report their age, gender, ethnicity, any disabilities, and first language.

#### Patient Activation Measure–Mental Health

The Patient Activation Measure–Mental Health (PAM-MH) is a patient-reported tool for measuring engagement in mental health care. The 13 items are used to measure patients according to 4 activation levels: skills, knowledge, confidence, and behaviors critical for coping with and managing mental health. Statements such as “When all is said and done, I am the person who is responsible for taking care of my mental health” will be rated using a 5-point response scale ranging from disagree strongly to agree strongly. PAM-MH was adapted from the physical health Patient Activation Measure; an examination of psychometric properties found it appears to be a reliable and valid measure [38]. It has been used in a number of studies with people accessing mental health services (see, for example, Matthias et al [39]). In the proposed feasibility trial, we will collect necessary parameters for planning a full prospective parallel cluster controlled trial to test the effectiveness of Power Up. We consider a minimal clinically important difference to be 55.10 on the PAM-MH in the management as usual arm (indicating they lack confidence to take action to manage their mental health difficulties) versus 67.10 in the Power Up arm (indicating they are able to take action to manage their mental health difficulties) [9].

#### CollaboRATE

CollaboRATE is a 3-item patient-reported shared decision- making measure. The measure assesses the extent to which an explanation of the health issue is given and patient preferences are elicited and integrated. A 10-point response scale from no effort was made to every effort was made is used to measure how much effort was made to “help you understand your health issue,” “listen to the things that matter most to you about your health issues,” and “include what matters most to you in choosing what to do next.” Concurrent validity with other shared decision-making measures and good interrater reliability have been demonstrated in a range of doctor-patient encounters [31]. However, its psychometric properties have yet to be tested in child mental health services. The authors of this study are involved in another study looking at the psychometric properties of CollaboRATE with children and young people.

#### Shared Decision Making Questionnaire

The Shared Decision Making Questionnaire (SDM Q-9) is a 9-item patient-reported shared decision-making questionnaire. Responders rate their agreement with 9 statements related to the decision-making process in healthcare consultations. One minor revision was made to the original version of the SDM Q-9; each item was changed from “my doctor” to “the clinician” to make the items applicable to any professional working with young people in CAMHS. Statements such as “The clinician made it clear that a decision needs to be made,” “The clinician helped me understand all the information,” and “The clinician and I selected a treatment option together” are rated on a 6-point response scale ranging from completely disagree to completely agree. The SDM Q-9 shows a high internal consistency (Cronbach alpha >.9), face validity, and high acceptance [40]. However, its psychometric properties have yet to be tested in child mental health services.

#### Experience of Service Questionnaire

The Experience of Service Questionnaire (ESQ) is a self-completion questionnaire that assesses children and young people’s views of services with respect to accessibility, humanity of care, organization of care, and environment. Responders rate their agreement with 13 statements, such as either “certainly true,” “partly true,” “not true,” or “don’t know.” The ESQ was developed and piloted with CAMHS attendees and has good precision in differentiating satisfaction with care on an individual level in this population [41]. For this study, 4 items of the ESQ will be used as a proxy measure of shared decision making: “I feel that the people who saw me listened to me,” “It was easy to talk to the people who saw me,” “My views and worries were taken seriously,” and “I have been given enough explanation about the help available there.” These items have previously been used as a proxy measure of shared decision making [14].

#### Youth Efficacy/Empowerment Scale–Mental Health

The Youth Efficacy/Empowerment Scale–Mental Health (YES-MH) assesses youth perceptions of efficacy with respect to managing their own mental health condition (self), managing their own services and supports (service), and using their experience and knowledge to help peers and improve service systems (system). The 7 items of the self subscale and 8 items of the service subscale will be used in this research. Responders rate their agreement with statements such as “I feel I can take steps toward the future I want” and “When a service or support is not working for me, I take steps to get it changed” on a 5-point response scale from almost or almost always to never or almost never. Initial analysis of the psychometric properties of this scale when used with 14- to 21-year-olds showed evidence of a clear factor structure and good internal reliability for the self subscale (Cronbach alpha=.88) and the service subscale (Cronbach alpha=.83) [42].

#### Strengths and Difficulties Questionnaire

The Strengths and Difficulties Questionnaire (SDQ) is a self-report behavioral screening questionnaire for children and adolescents measuring symptoms and functioning; 25 items capture 5 subscales, which measure emotional symptoms, conduct problems, hyperactivity/inattention, peer relationship problems, and prosocial behavior. Responders rate their agreement with statements such as “I get very angry and often lose my temper” as either “not true,” “somewhat true,” or “certainly true.” The impact supplement includes 8 items which inquire about chronicity of the difficulties, distress, social impairment, and burden to others. Responses to questions such as “Do the difficulties interfere with your everyday life?” are given using a 4-point response scale ranging from not at all to a great deal. Internal consistency has been judged as satisfactory; the mean Cronbach alpha was calculated as .73 [43]. The SDQ has been used with young people as a clinical assessment tool and in developmental, genetic, social, clinical, and educational research studies.

#### Client Receipt of Services Inventory–Children’s Version

The Client Receipt of Services Inventory–Children’s Version (CSRI) provides information on service utilization as reported by the main carer of the child in the family [44]. Information on background, household circumstances, employment and income, school support, and health service use is recorded regarding the retrospective period of 6 months. For each service type, the number and average duration of contacts is recorded. The CSRI has been previously used in child mental health contexts [45].

#### Dyadic OPTION Scale

This is a 12-item instrument to measure the extent to which patients have been involved in shared decision making from the viewpoint of the clinician. This instrument was adapted from the observer OPTION which underwent extensive psychometric testing. The 2 scales show convergent validity [46], and a systematic review has concluded that the dyadic OPTION scale is the most promising tool for measuring components of shared decision making [47]. Twelve statements, such as “A health problem was identified, where it was made clear that a decision was needed,” “Different options (including the possibility of doing nothing) were discussed,” and “It was made sure that information had been understood,” are measured on a 4-point response scale ranging from strongly agree to strongly disagree.

#### Acceptability Measures

Participants will also be asked to complete a questionnaire about the acceptability of all the above measures.

### Ethics and Informed Consent

Ethical approval has been obtained from Queen Square National Research Ethics Service and the Health Research Authority along with relevant local research governance and site-specific approvals. The trial has been registered with the ISRCTN registry [ISRCTN77194423] and ClinicalTrials.gov [NCT02987608].

Participant information sheets and informed consent forms will be given to all young people (assent forms for young people aged under 16 years), parents or carers, and clinicians. These forms were developed in conjunction with the Core Research Group and the Advisory Group, in particular the PPI coordinator and 2 representatives. The forms will inform participants that participation is entirely voluntary and that it will not impact their care if they decide not to take part. The risks and benefits to the participating people will be addressed and it will be made clear that the data obtained from the study will be confidential and their privacy ensured. Consent forms will also make the participant aware of their right to withdraw at any point during the research.

